## Abstract

**Background:**

Suicide risk of psychiatric patients has proven to be strongly increased in the months after discharge from a psychiatric hospital. Despite this high risk, there is a lack of systematic research on the causes of this elevated suicide risk as well as a lack of treatment and intervention for patients at high risk after discharge. The main objective of this pilot study is, firstly, to examine the factors contributing to the elevated *suicide risk* and, secondly, to investigate whether an additional setting of care starting at discharge may reduce *suicidality.*

**Methods:**

In this multi-centre pilot study, treatment as usual is complemented by an additional 18-month post-discharge setting of care for psychiatric patients at high risk for suicide. Two groups of patients differing in the amount of post-discharge personal contacts will be compared. One group of patients will be offered continuous personal contacts after discharge (months 1–6: monthly contacts; months 6–18: every 2 months) while another group of patients will receive contacts only at months 6, 12, and 18 after discharge. Data on suicidality, as well as associated with other symptoms, treatment, and significant events, will be collected. In the case of health-related severe events, the setting of care allows the patient to have the opportunity to connect with the doctor or therapist treating the patient.

**Discussion:**

The results of this study will contribute to identifying critical factors raising suicide risk after discharge and will demonstrate the potential influence on suicide prevention of a setting of care with regular personal contact after discharge.

**Trial registration:**

ZMVI1-2517FSB135 – funded by the German Federal Ministry of Health.

## Background

Approximately 800,000 people die by suicide globally every year [1]. According to the World Health Organization (WHO), the average suicide rate is 10.6 suicides per 100,000 persons in 2016 [2]. Europe’s average suicide rate is 15.4; the highest rate of all world regions.

Several programmes of the European Union focussed on reducing suicide rates. In Germany, a national suicide prevention programme (Nationales Suizidpräventionsprogramm, NaSPro) was initiated in 2002 by the German Association for Suicide Prevention (Deutsche Gesellschaft für Suizidprävention, DGS), and various activities were conducted.

To understand the heterogeneous and complex phenomenon of suicide, psychological autopsy studies have become a very valuable tool in past decades [3]. Up to 90% of people that died by suicide suffered from mental disorders. A systematic review of the literature showed proportions of mental disorders of 91% in 54 case series and 90% in 22 case-control studies [4]. A review of 27 psychological autopsy studies revealed a rate of 87.3% of all 3275 suicides that were diagnosed with a mental disorder prior to their death [5].

Periods of psychiatric inpatient treatment are considered as particularly vulnerable for suicide since hospitalisation only becomes necessary when symptomatology reaches a critical point, like patients who might endanger themselves or others. Suicide in hospitals was an object of investigation in various studies [6, 7]. Suicide risk is not the same across all treatment phases. The highest risk was measured during the months following a hospital stay. Though only a few data exist, they show remarkably similar results despite all differences in health care systems [8–13].

Investigations in Germany strongly revealed the highest risks of suicide for patients with schizophrenia and depression in the first months after discharge. In the 2 years following inpatient treatment, the risk to die by suicide was increased by a 66-time fold for male patients with schizophrenia, 110-time fold for female patients with schizophrenia, 111-time fold for male patients with depression, and a 41-time fold for female patients with depression [8].

A population-based study in the Oxford health region, UK, calculated the risk of suicide within 1 year after psychiatric discharge. Suicide rates were measured per 1000 person-years at risk and the standardised mortality ratio (SMR) for suicide. The SMR is a ratio of the observed number of deaths in a study group, and the number of deaths would be expected. The value among the general population was 1. For male patients, the SMR to die by suicide in the first 28 days after discharge was 213 (95% CI 137–317); the SMR for female patients was 134 (67–240). The suicide rate in the first 28 days after discharge was 7.1 (4.1–12) times higher for male patients and 3.0 (1.5–6.0) times higher for female patients than the level during the remaining 48 weeks of the first year after discharge [9].

A further study investigated suicide rates within a year of discharge from psychiatric inpatient care in Hong Kong. Discharges from all psychiatric hospitals or psychiatric wards in general hospitals from 1997 to 1999 were followed up for suicides and undetermined causes of deaths by record linkage with the Coroner’s Court. Suicide rates per 1000 person-years at risk and SMRs were calculated. In this study, 21,921 patients with an age of over 15 years were discharged from psychiatric hospitals from 1997 to 1999. Overall, 280 patients died by suicide within 1 year; 85 suicides (30%) occurred within 28 days after discharge. The SMRs for suicide in the first 28 days after discharge were 113 (95% CI = 86–147) for males and 178 (95% CI = 132–235) for females. These rates were 4.6 (95% CI = 3.2 to 6.3) times higher for males and 4.0 (95% CI = 2.7 to 5.6) times higher for females compared to the rate in the rest of the year [10]. A Korean study investigating suicide rates in the year following psychiatric discharge found that for all patients admitted to Seoul hospitals in Korea for psychiatric disorders between 1989 and 2006 (*N*, 8403), SMRs in the year following discharge were 49.7 for males and 45.5 for females [11].

A systematic review and meta-analysis on suicide rates after discharge examined publications from 1946 to 2016. Altogether, 100 studies were analysed that included 17,857 suicides. The pooled suicide rate was 484 suicides per 100,000 person-years (95% CI = 422–555). The suicide rate was highest within 3 months after discharge (1132; 95% CI = 874–1467). In the period from 3 months to 1 year, suicide rates were 654, 494 in the period after year 1 to year 5 and 366 for the follow-up period of 5 to 10 years, and 277 for studies with follow-up periods longer than 10 years [12].

A review on suicide rates following hospital discharge examined 48 studies from 1964 to 2017. The pooled annualised suicide rate was 241 (95% CI = 238–243) per 100,000 person-years including 41 studies [13].

Several causes of this excessively increased suicide risk in the months after discharge may be considered as follows:
Patients were not treated successfully. There was treatment failure or only a partial response to treatment.New or different problems developed after discharge that overburdened the individuals’ potentially reduced coping strategies.Because of other reasons, clinical symptoms worsened, for example, due to a lack of adherence to medication.The influence of the therapeutic relationship—usually ending with discharge. To date, there have been only a few studies and statistically reliable results. One study analysing German railway suicides showed an odds ratio of 22.86 for the change of therapist during the hospital stay and the association with suicide [14].Other causes such as disappointment and hopelessness after failing the highest level of care, the associated stigma of being admitted to a mental health facility, being in contact with patients that are potentially very sick, and learning about other more lethal methods of suicide.

The group of patients being discharged from a psychiatric inpatient stay represents a population at risk for suicide that does not receive specialised care regardless of the type of mental disorder. Specific care concepts focussing on these patients with tremendously increased suicide risk rarely exist.

Moreover, systematic investigations on the complex and heterogeneous background of increased suicide mortality after discharge from psychiatric hospitals and the influences of different treatment settings on suicide prevention were not carried out.

For this reason, the presented study examines the following questions:
i)What might influence the increased suicide mortality in the months after discharge from an inpatient psychiatric hospital stay? Which factors might influence suicide mortality?ii)Is it possible to reduce suicidality after discharge by establishing a specific setting of care?

This project is of considerable socio-political interest. If it is possible to reduce suicide rates or suicidal behaviour by implementing a specific setting of care, this concept might be transferred to other mental health systems.

## Methods/design

The objective of this multi-centre trial is, firstly, to identify factors affecting suicide risk after psychiatric discharge and, secondly, to investigate whether a specific setting of care defined by regular personal contacts influences the elevated suicide risk after discharge from a psychiatric hospital.

This naturalistic study will allocate patients with schizophrenia, schizotypal and delusional disorders (ICD-10: F2), or mood disorders (ICD-10: F3) [15] as principal diagnosis either to a group with only a single contact 6, 12, and 18 months after discharge or to a group where personal contacts are organised monthly to every 2 months in the 1.5 years following discharge. These study contacts are an addition to treatment as usual for all patients and do not include medical or therapeutic treatment. Following discharge, the protocol will continue even if the patient gets admitted to the hospital again. By-phone visits will be allowed as alternatives.

The hypothesis to be tested is whether a specific setting of care reduces the suicide risk and does this particular setting of care plus regular treatment as usual lead to a significant reduction of suicidality compared to a less intense setting of care plus regular treatment as usual in the months following a psychiatric hospital stay.

The primary endpoint of the study is the evaluation of suicidality. Suicidality is measured by the score of the clinician-administered Sheehan Suicidality Tracking Scale (S-STS, [16]) at 6, 12, and 18 months after discharge.

Secondary endpoints include the score of the patient self-reported S-STS, changes in depressive symptoms as indicated by the Montgomery Asberg Depression Rating Scale (MADRS, [17]), changes in psychotic symptoms as indicated by the Brief Psychiatric Rating Scale (BPRS, [18]), and changes in the Visual Analogue Mood Scale (VAMS, [19]) at 6, 12, and 18 months after discharge. Due to the possibility of contacting the doctor/therapist and/or a close person of the patient in case of non-appearance to an appointment combined with failure, to reach the patient, we want to gain information about the state of health and ascertain possible suicides. At every study visit, it is asked for suicide attempts.

The number of days of psychiatric hospital treatment, as well as quantity and dosage of medication and the number of psychotherapy sessions, will be recorded. Furthermore, critical stress-related events after discharge and the subjective degree of stress will be collected.

Basic descriptive data on regional health care services/differences at the four participating hospitals will be collected (e.g., number of patients presenting with disorders of F2 and F3-section (ICD-10), regional characteristics, differences in networks of psychiatric support, and treatment after discharge). Recruitment started in 2018 and will end in 2021.

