### Study population and eligibility

Patients will be recruited from the four participating psychiatric hospitals in Germany (Department of Psychiatry and Psychotherapy, University Hospital Carl Gustav Carus, Dresden; Municipal Hospital Dresden, Department of Psychiatry and Psychotherapy, Dresden; Department of Psychiatry, Psychotherapy and Psychosomatics University Hospital Halle; Department of Psychiatry and Psychotherapy Furtbach Hospital, Stuttgart). All patients meeting the inclusion criteria will be informed about the study. Inclusion criteria are 18 years of age and older, admitted as an inpatient, presenting with either a mood/affective disorder (F3 section of ICD-10) or schizophrenia, schizotypal or delusional disorder (F2 section of ICD-10) and written informed consent. Patients agreeing to participate in the study have a choice to which group they want to belong to. A randomised allocation is not made for ethical reasons. Patients with legal guardians are excluded from the study. Patients are not given any incentive or compensation for participation.

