### Power analysis and sample size calculation

The presented multi-centre trial is designed as a pilot study. We, therefore, did not conduct a statistical power analysis or sample size calculation. Yet, we estimate a minimum of 300 patients treated with ICD-10 F2- or F3-diagnosis in each study centre every year. Based on clinical experience, we strive for at least 100 patients per study centre.

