### Statistical analysis

Descriptive statistics covering sociodemographic and clinical baseline data will be reported using proportions, means, and standard deviations as well as Chi-square tests, *t* tests, and Mann-Whitney tests as appropriate. Results will be presented with 95% confidence intervals where applicable. Proportions of adverse events will be summarised. Sociodemographic and clinical variables that differ significantly between groups at baseline will be included as covariates in further analyses. To identify potential explanatory variables on suicidality in the weeks and months after discharge, a potential correlation of variables will be assessed by frequencies, percentages, means and standard deviations, correlation coefficients, etc. Variables that are identified as potentially influencing suicidality will be included as factors in further analyses.

Normal distribution will be assessed by Shapiro-Wilk tests and by visual inspection of histograms. Homogeneity of variances will be assessed using Levene’s test.

Statistical tests will be two-sided using an alpha level of 0.05. All analyses will be conducted using IBM SPSS Statistics for Windows, version 25.

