The present study has several limitations. First, patients with a principal diagnosis of only categories F2 and F3 of ICD-10 (schizophrenia, schizotypal or delusional disorders, depression, bipolar disorder) will be included. In contrast, all other diagnoses will be accepted as comorbidities only. This procedure leaves out several groups of patients. We tried to restrict the heterogeneity of our study population in favour of receiving insights that are more meaningful for a well-defined group of patients at this first step of approaching very critical aspects of suicidality. Second, a bias may arise from the fact that patients have a choice of which group they would like to be placed in, either group 1 or group 2. On the other hand, this choice can offer useful insights into real-world clinical aspects by reflecting patients’ different characteristics as well as needs and motivation to make use of suicide prevention measures providing personal contact. This is in line with the ethical requirements of not withholding any condition from participants.

As a limitation of our study, we do not examine developments during the first days after discharge. The first study contact is scheduled 1 month after discharge. A recently published meta-analysis comprising 34 publications showed a pooled estimate of the suicide rate of 2950 suicides per 100,000 person-years (95% CI = 1740–5000) [28]. The pooled estimate of the suicide rate during the first month after discharge was 2060 per 100,000 person-years (95% CI = 1300–3280).

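### The hypothesis is causal, but with self-chosen groups the ANCOVA tests an adjusted difference between choosers, so the 0.05 level is not assured for the hypothesis as stated

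*Protocol article*

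**What the plan says.** Methods/design in the protocol article gives the hypothesis to be tested. It asks "does this particular setting of care plus regular treatment as usual lead to a significant reduction of suicidality" compared with a less intense setting. The Discussion paragraph of the Abstract says the results "will demonstrate the potential influence on suicide prevention of a setting of care with regular personal contact after discharge".

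Allocation is not randomised, for ethical reasons. Study population and eligibility states: "Patients agreeing to participate in the study have a choice to which group they want to belong to".

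Primary outcome measures specifies an ANCOVA of the clinician-administered S-STS. It adjusts for baseline variables that differ significantly between groups and for potentially influencing risk factors. The level is set under Statistical analysis: "Statistical tests will be two-sided using an alpha level of 0.05".

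The Discussion acknowledges that patient choice may cause bias. It then describes the choice as informative "by reflecting patients’ different characteristics as well as needs and motivation to make use of suicide prevention measures".

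Course and Assessments list the baseline data: demographics, substance use, psychiatric and medical history and treatment, personal and family history of suicidality, symptom scales, and questionnaires on perfectionism, personality and resilience. Need or motivation for contact, or the reason for choosing a group, is not in that list.

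**The concern.** Two null hypotheses are in play. The stated one is that additional contacts do not reduce suicidality. The one the ANCOVA tests is that chosen group is unrelated to S-STS given the covariates in the model. They coincide only if no unrecorded characteristic influences both the choice and the outcome.

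The article itself gives a reason to doubt this. Need for support and motivation to use it plausibly predict later suicidality, and the article says the choice reflects them. The limitation is disclosed in the Discussion, but nothing is carried back to the hypothesis in Methods/design or to the test in Primary outcome measures.

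A difference due to selection could therefore be attributed to the contacts. If motivated, lower-risk patients choose more contacts, selection looks like benefit. If patients who feel at risk choose them, selection looks like harm or hides a real benefit. The Background foresees transferring the concept to other mental health systems, so either error would matter.

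This is separate from how measured covariates are picked. It concerns what remains after adjustment for everything in the model.

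**Working it through.** **Inputs from the protocol article**
- Two-sided alpha 0.05 (Statistical analysis).
- Four centres: "Patients will be recruited from the four participating psychiatric hospitals in Germany". Target: "we strive for at least 100 patients per study centre". So N = 4 × 100 = 400.
- No planned power to compare against: the authors "did not conduct a statistical power analysis or sample size calculation".

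**Assumptions, not in the article**
- Group split: 200/200, with 80/320 as an uneven case.
- Loss to follow-up: none, or 30%, which leaves 400 × 0.7 = 280, split 140/140.
- Residual selection shift *d*: the S-STS difference between choosers that remains after adjustment when the contacts do nothing, in residual SD units. Range 0 to 0.30.

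**Formula**
- SE = √(1/n₁ + 1/n₂) in SD units; δ = d/SE.
- Rejection = P(|T| > t₀.₉₇₅), with T non-central t, df = N − 3, non-centrality δ.
- Normal approximation: 1 − Φ(1.96 − δ) + Φ(−1.96 − δ).

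Standard errors:
- 200/200: √(1/200 + 1/200) = 0.100
- 80/320: √(1/80 + 1/320) = 0.125
- 140/140: √(2/140) = 0.1195

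**The plan's own figure.** With d = 0, rejection is 0.050, so the stated alpha holds when there is no residual selection.

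**With residual selection and no contact effect**

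| Split | d = 0.05 | 0.10 | 0.20 | 0.30 |
|---|---|---|---|---|
| 200/200 | 0.079 | 0.170 | 0.514 | 0.849 |
| 80/320 | 0.068 | 0.126 | 0.358 | 0.668 |
| 140/140 | 0.070 | 0.133 | 0.385 | 0.706 |

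The normal approximation agrees closely (for example 0.516 and 0.851 at 200/200 for d = 0.20 and 0.30).

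**Direction.** At 200/200 and d = 0.10, δ = 1.0. Rejection in the direction of the shift is 1 − Φ(0.96) = 0.1685; in the opposite direction it is Φ(−2.96) = 0.0015. The total of 0.170 is therefore almost all one-sided. It is a false benefit only if selection favours the group with more contacts. If selection runs the other way, false findings of benefit fall to about 0.15%, and nearly all rejections point to harm.

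**Does adjusting for a measured baseline remove the problem?** ANCOVA was simulated with N = 400, 4,000 runs per cell and no contact effect. A measured baseline (coefficient 0.5) was in the model. An unmeasured factor drove both choice (odds ratio per SD) and outcome (standardised effect).

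| Choice OR | effect 0.1 | 0.2 | 0.3 | 0.4 |
|---|---|---|---|---|
| 1.25 | 0.055 | 0.080 | 0.121 | 0.175 |
| 1.5 | 0.082 | 0.142 | 0.268 | 0.454 |
| 2 | 0.107 | 0.298 | 0.576 | 0.832 |

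- With choice unrelated to the factor (OR 1), rejection is 0.046 to 0.056.
- If the factor correlates 0.3 with the measured baseline, the OR 1.5 row barely changes: 0.069, 0.127, 0.259, 0.438.
- If the factor is measured and always in the model (OR 1.5, effect 0.3), rejection is 0.057 instead of 0.268.
- If it is measured but enters only when its baseline difference is significant, rejection is 0.044 to 0.059 over effects of 0.2 to 0.4.

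In these scenarios the excess comes from what is not in the data, not from the rule for choosing among recorded covariates.

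**The case against.** The other side has several sound points.

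*Disclosure and tone.* The article calls the study naturalistic and a pilot, states that allocation is not randomised, and names self-selection as a limitation. Elsewhere it is softer: the Discussion asks only whether a contact setting may be a promising prospect, and the Abstract speaks of a potential influence. A reader might infer that the authors will draw a causal conclusion from p < 0.05. No section says so. What stands is narrower: the hypothesis to be tested is worded causally, and the disclosure leaves both it and the test unchanged.

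*Strength of selection.* A reader might infer that the test does reject far too often. The documents do not support that, since they give no strength of selection. A weak shift of 0.05 SD gives only about 7 to 8%, and the simulated rates run from about 0.05 to 0.83. Inflation is possible and can be large, but it is not shown.

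*Motivation not measured.* A reader might also infer that need and motivation go unrecorded. The article condenses a fuller protocol, so one can say only that no such item is listed. Recorded severity, suicidality history, personality and resilience may capture part of the selection.

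*Missing sensitivity analysis.* This may sit in an analysis plan that is not shown, so its absence is not held against the article. It is proposed below as a remedy for the mismatch.

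**Conclusion.** The point holds as a mismatch between the stated hypothesis and what the stated design and test can address. The ANCOVA p-value concerns an adjusted difference between patients who chose more and fewer contacts. It bears on the effect of the contacts only under no unmeasured confounding, an assumption the article does not state and its own Discussion makes doubtful.

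The 0.05 level is therefore not assured for the hypothesis in Methods/design. With no contact effect and assumed shifts of 0.05, 0.10, 0.20 and 0.30 SD, two-sided rejection would be about:
- 8%, 17%, 51% and 85% with 200/200 analysed;
- 7%, 13%, 36% and 67% with 80/320;
- 7%, 13%, 39% and 71% with 140/140.

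These rest on the assumed shift, split and loss, and on approximately normal residuals. Direction is open, so they are not rates of false benefit. Because hypothesis and test are both in the text, the matter should be corrected; pilot status does not remove it, since a formal hypothesis and alpha are set.

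**What to change.** 1. In Methods/design and the Discussion paragraph of the Abstract, state the group result as the covariate-adjusted difference in S-STS between patients who chose more and fewer contacts, with its 95% CI. Say that reading it as an effect of the contacts requires no unmeasured confounding.

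2. In Primary outcome measures, add a prespecified sensitivity analysis. Report the residual selection shift, in S-STS points and in SD, that would move the estimate to zero (the estimate itself) and the nearer CI limit to zero (|estimate| − 1.96 × SE). Show beside it, as a descriptive benchmark only, the shifts attributable to measured baseline variables, for example the change in the adjusted difference when each is left out. Set no pass/fail rule. As an illustration, an adjusted difference of 0.30 SD at 200/200 has a CI limit of 0.30 − 1.96 × 0.10 = 0.104 SD. A selection shift of about 0.10 SD would remove significance, and one of 0.30 SD would remove the difference.

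Adding a baseline question on the reason for the choice and using it as a fixed covariate is not recommended. Recruitment began in 2018 and the baseline visit precedes discharge, so the answer would be missing for patients already enrolled. The reason may also nearly determine the group, leaving little overlap for adjustment.

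The cost is a few sentences, a little more analysis and a more cautious conclusion. Patient choice and its ethical rationale are untouched.
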